#### Data management

To enhance data quality, a double-coding process will be employed for all participants, where all data will be coded independently and reviewed twice to ensure accuracy and consistency.

#### Statistical methods

Analysis will undergo using the Statistical Package for the Social Sciences software (SPSS version, 22). The significance levels of α and β will be set at 5% and 10%, respectively, while the confidence interval will be established at 95%. To compare the research variables before and after the intervention, the paired t-test or its non-parametric equivalent will be utilized. The normality of the data will be checked using the Kolmogorov- Smirnov test. One-way ANOVA with Tukey’s post hoc test will be employed to compare the quantitative variables in the study. ANCOVA will be used to eliminate any intervening variables. The Kruskal-Wallis and Mann-Whitney tests will be used to evaluate groups of quantitative variables in non-parametric conditions. For within-group analysis, repeated measures ANOVA will be conducted when initial homogeneity and normality of data are met. If initial homogeneity is established without normality of data distribution, the Friedman test will be used. A linear mixed model adjusted for the baseline variables will be employed when initial homogeneity is not found. Per protocol analysis principles will be applied in the study. Additionally, univariate analysis and multiple regression analysis will be conducted to identify the predictor factors that influence prism effectiveness in presbyopic patients.

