#### Outcomes

The primary outcomes we focused on were the improvement in NPC and NPFV measures at break and recovery points, and the secondary outcomes were improvements in Convergence Insufficiency Symptom Survey (CISS) score, vergence facility, near heterophoria, stereopsis, prism adaptation, NNFV, that will be assessed before and after the intervention and comparison will be done among the groups. These primary and secondary goals are directly related to objective and subjective aspects of convergence insufficiency respectively.

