### Sample recruitment

#### Methods: assignment of interventions (for controlled trials)

To allocate patients to the randomized treatment groups, the patients will be categorized based on their age, gender, and the severity of their CI using random blocks. We will have 3 groups: control group, prism prescription group, and home vision therapy group. To generate a list of random numbers, the website www.random.org will be utilized. Consecutive numbers generated by the website (ranging from 1 to 150) will be assigned randomly to patients in each of the group by optometrist [name], who has no prior knowledge of the random numbers list. The optometrist responsible for intervention, [name], will be the only person who has access to the random numbers list. Due to the nature of vision therapy and other training instructions provided to the subjects, this optometrist will not be blinded. So participants get assigned consecutive numbers and then the randomized assigns treatments to each number. 1 optometrist applies the treatment. The other masked optometrist makes the measurements. Consequently, the allocation concealment will be ensured because the optometrist in charge of recruitment will be unaware of the group to which the subject will be assigned.

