### Methods: data collection, management, and analysis

#### Data collection

To enhance data quality, measurements will be conducted twice during each session, and the modified questionnaires will undergo evaluation for their suitability among adults with presbyopia in terms of reliability and validity. This assessment will take place during the phase one of the study. In order to enhance participant retention and ensure successful follow-up, we will establish communication with the participants and provide encouragement to continue with the prescribed exercises. Moreover, in home vision therapy group, the patients are provided with a form to record the duration of their home exercises.

The optometrist responsible for recruitment in this study, [name] will conduct all the assessments. Throughout the study, [name] will maintain blindness regarding the group to which the subject has been assigned.

Table 1 displays the potential values and demographic variables of the subjects. The following variables will be recorded at the start of treatment: age, gender, distance best corrected visual acuity, near best corrected visual acuity, dry refraction, cycloplegic refraction, presence of dry eye, inter-pupillary distance and medications that may affect accommodation and vergence.

**Table 1 Tab1:** Potential values and demographic variables

Variable	Values
Age	Years
Gender	Male/Female
Distance best corrected visual acuity	Log MAR
Near best corrected visual acuity	Log MAR
Dry refraction	Diopter
Cycloplegic refraction	Diopter
Dry eye	Yes/No
Medication	Yes/No
Inter-pupillary distance	Millimeter

MAR: minimum angle of resolution

Table 2 displays the measuring tool used, assessment time, and outcome variables. A single experienced optometrist ([name]), who is also responsible for recruitment, will conduct all assessments. The optometrist conducting the assessment will be blinded to the group assigned to each participant.

**Table 2 Tab2:** outcome variables

Outcome variables	Assessment time			Measuring tool
	Baseline	1 month post treatment	2 month post treatment	
Convergence insufficiency	*	*	*	CITT definition [17]
Vergence facility	*	*	*	Prism flipper
Distance heterophoria	*	*	*	Prism cover test
Near heterophoria	*	*	*	Prism cover test
Stereopsis	*	*	*	TNO test
Prism adaptation	*	*	*	Prism trial lens
Near positive fusional vergence (blur point)	*	*	*	Prism bar
Near positive fusional vergence (break point)	*	*	*	Prism bar

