Vergence facility will be assessed using a flipper prism (3 base in and 12 base out), with the target set at two lines above the best near-corrected visual acuity (20/30). The test will be conducted with the patients near glasses on and recorded at a distance of 40 cm. The distance heterophoria will be assessed by means of prism bar and alternate cover test with the digital Snellen chart set at 20/30 raw with a single letter at a distance of 6 m. The near heterophoria will be assessed by means of prism bar and alternate cover test and over the patients near glasses with a 20/30 single optotype set at 40 cm. Stereopsis will be evaluated using the TNO test with red-green filters and the patients near glasses at 40 cm. Near negative fusional vergence, with a rate of 2 prisms per second, will be obtained using prism bar and a 20/30 single E chart set at 40 cm over patients near correction (in the blur, break and recovery points). Prism adaptation will be checked by measuring the amount of heterophoria one hour after wearing the glasses, and the percentage change in heterophoria will be recorded as prism adaptation. Near positive fusional vergence (in the blur, break, and recovery point) will be measured using a base-out prism bar with a 20/30 column set at 40 cm and the patients near glasses with a rate of 2 prisms per second. The modified CISS questionnaire will be used to assess the frequency and type of symptoms before and after treatment. The near point of convergence will be evaluated using the red-green filters and accommodative target methods. A penlight will be brought close to the patient’s face, and the patient will be asked to report the diplopic image as soon as possible. This point will be recorded as the break point. The examiner will then increase the distance between the penlight and the patient’s face until a single image reappears, which will be recorded as the recovery point. The near point of convergence will be measured three times, and the results will be averaged. The near point of convergence will be recorded based on both the break and recovery points, with the patient wearing their near glasses. In the accommodative target method, participants will be guided to maintain visual singularity while a single target with a 20/30 visual acuity will be gradually brought closer to them. The movement of the target will persist until diplopia is reported or the examiner detects an objective loss of binocular vision. The target will then be moved backward until either the participant subjectively reports single vision or the examiner objectively observes the restoration of binocularity.

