
To ensure that the optometrist conducting the clinical testing remains unaware of the prism near spectacles, in follow up visits, all glasses will be examined in a separate unit by another optometrist and [name] will not investigate the new habitual spectacles.

To ensure and encourage adherence, a written log detailing the daily usage of near spectacles, including approximate durations and descriptions of home exercises, will be maintained. In addition, video calls will be conducted to monitor and promote compliance. Participants are strongly encouraged to remain engaged in the study. Individuals who have successfully finished the study will receive the spectacle prescription at no cost. In the event that a participant is unable to continue or cooperate, they will be replaced by another individual.

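### The ANCOVA covariates are described by a wrong and open-ended term; the arm comparison should be tied to baseline covariates only (minor)

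*Protocol article*

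**What the plan says.** The protocol article, Statistical methods, sets out the comparison of arms in two adjacent sentences: "One-way ANOVA with Tukey’s post hoc test will be employed to compare the quantitative variables in the study", and then "ANCOVA will be used to eliminate any intervening variables". No covariate is named for the ANCOVA.

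The section mentions baseline adjustment in one other place, after the within-group methods and under a condition: "A linear mixed model adjusted for the baseline variables will be employed when initial homogeneity is not found".

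Variables fixed before treatment are described elsewhere. Under assignment of interventions, "the patients will be categorized based on their age, gender, and the severity of their CI using random blocks". Under Data collection, "The following variables will be recorded at the start of treatment: age, gender, distance best corrected visual acuity", followed by other background items. Table 2 schedules every outcome at baseline, one month and two months.

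The trial also collects quantities after randomisation. For adherence, "a written log detailing the daily usage of near spectacles, including approximate durations and descriptions of home exercises, will be maintained". For the prism measure, heterophoria is re-measured after an hour of wearing the glasses and "the percentage change in heterophoria will be recorded as prism adaptation".

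On the outcomes that the comparison serves: "The primary outcomes we focused on were the improvement in NPC and NPFV measures at break and recovery points".

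**The concern.** Adjustment in a randomised comparison is useful when the covariate was fixed before allocation. It then explains outcome variation and corrects chance imbalance without changing the effect being estimated. A covariate that treatment can alter is different: conditioning on it takes out whatever part of the effect runs through it, and the arms are then compared at equal levels of something that treatment produced.

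The sentence names the second kind. Its word for the covariates means variables on the path from treatment to outcome, and it covers any of them. Candidates are in the data set: logged spectacle wear, exercise time, follow-up prism adaptation and the one-month readings. An analyst who entered one of these could say that the plan allows it.

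The wording matters more because no other sentence fixes baseline adjustment for the arm comparison. The one reference to baseline variables belongs to a mixed model that is used only if the groups differ at the start. Unless that happens, the stated comparison is unadjusted, although the baseline values and stratification factors are all collected.

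**Working it through.** **1. Which sentence governs which covariates**

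| Sentence in Statistical methods | Covariates | When used |
|---|---|---|
| One-way ANOVA with Tukey | none | default arm comparison |
| ANCOVA | those called intervening, not listed | not stated |
| Linear mixed model | baseline variables | only if initial homogeneity is not found |

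Where the authors mean baseline they write baseline, as in the mixed-model sentence. The ANCOVA sentence uses a different word, and no text links the two. The baseline reading is therefore plausible but not secured. Equally, no section places the adherence log, exercise time, prism adaptation or one-month values in the ANCOVA.

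**2. The plan's own figure**

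Inputs from Sample size calculation: means 17, 16 and 21.52 cm, SD 7.50, α = 0.05, power 90%, dropout 15%, 50 per group.

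- Mean of means = (17 + 16 + 21.52)/3 = 18.173.
- Squared deviations: 1.377 + 4.723 + 11.200 = 17.300.
- f = √(17.300/3)/7.5 = 2.401/7.5 = 0.320 (the article states 0.311).
- One-way ANOVA, three groups, noncentral F: f = 0.320 needs 43 per group (power 0.906).
- Dropout: 43/0.85 = 50.6, so 51; or 43 × 1.15 = 49.5, so 50.

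The stated 50 is reproduced to within one patient. With the stated f of 0.311 the requirement is 45, which becomes 53 or 52; that small discrepancy does not bear on this point. The calculation uses no covariate, so it says nothing about which ANCOVA was intended.

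**3. What baseline-only ANCOVA would give**

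Residual SD = 7.5 × √(1 − ρ²), where ρ is the correlation between baseline and final near point of convergence. The article gives no ρ, so a range is assumed. Power is for the same F test with f/√(1 − ρ²) at 42 per group (50 × 0.85 = 42.5, rounded down).

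| ρ (assumed) | Residual SD, cm | Power at 42 per group |
|---|---|---|
| 0 | 7.50 | 0.899 |
| 0.3 | 7.15 | 0.925 |
| 0.5 | 6.50 | 0.965 |
| 0.7 | 5.36 | 0.996 |

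**4. If the unadjusted ANOVA is run on improvement from baseline**

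The primary outcomes are worded as improvement, so change scores are possible. With equal SDs at both visits (assumed), the SD of change = 7.5 × √(2(1 − ρ)): 8.87, 7.50 and 5.81 cm for ρ = 0.3, 0.5 and 0.7. The ANCOVA values of 7.15, 6.50 and 5.36 cm are smaller in each case, so the gain does not depend on which form of the outcome is used.

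**The case against.** The strongest reply is that this is loose English and not a planned analysis. To eliminate a variable is how people speak of nuisance or confounding factors. The only adjustment set that the section names is baseline variables, and the article lists obvious baseline candidates. The quantities that could act as mediators have other stated roles: prism adaptation is a secondary outcome and is also scheduled at baseline, the one-month readings are scheduled outcome measurements, and the log exists to support adherence. The unadjusted ANOVA remains and would still show the total effect. A covariate list is something that an article may leave to the fuller plan.

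Most of this stands. A reader might infer that the trial will adjust for wear time, exercise time, prism adaptation or one-month values, and so understate a treatment or reorder the arms. The article does not support that: it names no such covariate, and any figure for the loss would rest on an assumed mediator and an assumed mediated share.

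The reply does not dispose of the wording. The objection here is not that a list is absent, but that the class of covariate is named wrongly and without limit. Nor does the ANOVA settle the matter, because the section does not say which result governs if the adjusted and unadjusted comparisons disagree.

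**Conclusion.** The point holds in a limited form, and its severity is minor. The ANCOVA sentence uses a term that strictly means on-path variables and leaves it open-ended, so a literal reading allows covariates measured after randomisation. Baseline or nuisance variables were probably intended. Bias in the treatment effect is a possibility that the wording leaves open, not something the plan is shown to contain, and no size in centimetres should be attached to it.

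The firmer part is that baseline adjustment of the arm comparison is nowhere fixed as the default. Fixing it would keep the same target effect. Under assumed correlations of 0.3 to 0.7 it would cut the residual SD from 7.5 cm by about 5% (7.15/7.5 = 0.95) to 29% (5.36/7.5 = 0.71). These figures rest on the article's SD, on the assumed correlations and on a linear relation between baseline and outcome. They cover near point of convergence only, since Sample size calculation gives no SD for fusional vergence.

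**What to change.** Replace the ANCOVA sentence in Statistical methods with:

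> The arm comparison is an ANCOVA adjusted for the baseline value of the outcome and the stratification factors (age, gender, CI severity), whether or not baseline homogeneity is found; no variable measured after randomisation is a covariate in it, and any analysis using one is exploratory.

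The ANOVA and mixed-model sentences should then be edited so that they do not compete with this rule as the default arm comparison.

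The cost is a short text change. The baseline outcomes and stratification factors are already collected, so it needs no new data, no extra visit and no change to the sample size. Under Trial status, 121 of 150 patients had been randomised by 3 October 2023; the change can still be made and dated before the arms are compared.

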#### Sample size calculation

To calculate the appropriate sample size for all outcome variables specially those related to primary outcomes, a two-tailed test with α = 5% and β = 10% and 90% power was conducted using the Power Analysis & Sample Size software (PASS, version 11). The selection of appropriate statistics for the sample size determination was based on three previous studies [10, 12, 13]. The sample size in each group was determined using the One-way ANOVA menu of PASS 21 software, taking into account the quantitative nature of the dependent variables and the presence of three groups. The test was conducted with a first type error (α) of 0.05 and a second type error (β) of 0.1, corresponding to a test power of 90%. The mean values of 17 cm, 16 cm, and 21.52 cm, along with a standard deviation of 7.50, were extracted for NPC, and the effect size was calculated as 0.311. Considering a 15% dropout rate, the total number of samples in each group amounted to 50, resulting in a combined total of 150 samples.

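### Pre-tests on the trial data choose the analysis, and no baseline-adjusted primary comparison of the arms is secured

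*Protocol article*

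**What the plan says.** All of the following is in the protocol article, Statistical methods.

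- **Comparison of arms.** Normality is checked with Kolmogorov-Smirnov. Quantitative variables are compared by one-way ANOVA with Tukey's post hoc test, or by Kruskal-Wallis and Mann-Whitney if the data are judged non-normal. No baseline term is stated for either.
- **Branches introduced as within-group.** "repeated measures ANOVA will be conducted when initial homogeneity and normality of data are met"; the Friedman test is used if there is homogeneity without normality; and "A linear mixed model adjusted for the baseline variables will be employed when initial homogeneity is not found". Initial homogeneity is not defined.
- **Other adjustment.** "ANCOVA will be used to eliminate any intervening variables". The covariates, the outcomes and the circumstances are not given.
- **Before-after comparison.** "the paired t-test or its non-parametric equivalent will be utilized".

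Elsewhere, the Outcomes section makes improvement in NPC and near positive fusional vergence, at break and recovery, primary. The Objectives section names three between-arm comparisons. Table 2 shows every outcome measured at baseline, 1 month and 2 months. The assignment section stratifies randomisation by age, gender and severity of convergence insufficiency.

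**The concern.** No single primary analysis is named. Instead, properties of the collected data select the method, so two primary outcomes could end up tested differently, one on means and the other on ranks. Unlike the mean comparison, a rank test gives no difference in centimetres or prism dioptres, and as listed here it takes no baseline covariate.

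The homogeneity condition is a poor trigger for adjustment. In a randomised trial, arm differences at baseline are chance by construction, so a test of them answers no useful question. The reason to adjust is that baseline predicts follow-up, and this holds whether or not the arms happen to differ. A rule that adjusts only after a failed homogeneity check leaves most of the available precision unused, although the baseline values are measured anyway.

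The before-after tests raise a smaller issue. Entry requires a remote NPC, inadequate fusional vergence and a symptom score above a cut-off, so regression to the mean can produce apparent improvement in any arm.

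**Working it through.** **Inputs from the documents (Sample size calculation).** NPC means and SD: "The mean values of 17 cm, 16 cm, and 21.52 cm, along with a standard deviation of 7.50, were extracted for NPC". Error rates: "The test was conducted with a first type error (α) of 0.05 and a second type error (β) of 0.1". Dropout 15%; 50 per arm; one-way ANOVA with no covariate.

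**Assumptions.** (a) The baseline/follow-up correlation ρ is not in the documents; 0.3, 0.5 and 0.7 are used. (b) Initial homogeneity is read as a 5% test of arm differences at baseline.

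**Step 1: the plan's own figure.** The grand mean is (17 + 16 + 21.52)/3 = 18.173. The squared deviations are 1.377, 4.723 and 11.200, with mean 5.767 and square root 2.401. So f = 2.401/7.50 = 0.320. (The article states that "the effect size was calculated as 0.311", which differs slightly from its own means and SD.) With non-centrality λ = 3·n·f², 90% power needs n = 43 per arm: λ = 129 × 0.1025 = 13.22, power 90.6%; n = 42 gives 89.9%. Allowing for dropout, 43/0.85 = 50.6, so 51; or 43 × 1.15 = 49.5, so 50. The stated 50 per arm is reproduced. The printed f of 0.311 would give 45 per arm, or 52 to 53 with dropout. The rest uses f = 0.320 and n = 43.

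**Step 2: how often the gate opens.** A 5% baseline test flags 5% of randomised trials per variable, about 1 in 20. For four independent variables, the chance of at least one flag is 1 − 0.95⁴ = 18.5%. Stratifying by severity makes a flag on related variables rarer still.

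**Step 3: what adjustment is worth.** The residual SD becomes 7.50·√(1 − ρ²), so λ becomes 13.22/(1 − ρ²). For an analysis of change from baseline, the SD is 7.50·√(2(1 − ρ)).

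| | ρ = 0.3 | ρ = 0.5 | ρ = 0.7 |
|---|---|---|---|
| ANCOVA standard error relative to unadjusted follow-up | 0.95 | 0.87 | 0.71 |
| λ with ANCOVA | 14.5 | 17.6 | 25.9 |
| Power, unadjusted follow-up | 90.6% | 90.6% | 90.6% |
| Power, change score | 78.1% | 90.6% | 99.0% |
| Power, ANCOVA | 93.1% | 96.9% | 99.7% |
| n per arm for 90% power, ANCOVA (unadjusted: 43) | 39 | 32 | 23 |

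**Step 4: what the conditional rule recovers.** In 20,000 simulated trials per setting (43 per arm, normal data, planned means, omnibus F test), the arms were compared unadjusted unless the baseline test gave p < 0.05, and by ANCOVA otherwise.

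| | ρ = 0.3 | ρ = 0.5 | ρ = 0.7 |
|---|---|---|---|
| Never adjust | 90.73% | 90.77% | 90.66% |
| Adjust only if flagged | 90.87% | 91.17% | 91.52% |
| Always adjust | 93.04% | 96.65% | 99.63% |
| Share of gain recovered | 0.14/2.31 = 6% | 0.40/5.88 = 7% | 0.86/8.97 = 10% |

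If the unadjusted branch analyses change instead, the rule has 78.6%, 91.3% and 99.1% power, still below always adjusting.

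**Step 5: type I error.** Under no arm difference, the rule rejects in 5.0%, 4.5% and 3.6% of trials, so the homogeneity gate does not inflate the error rate. The normality gate was not simulated.

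**The case against.** Several points on the other side have force.

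- **ANCOVA is planned without a condition.** True, and baseline is not excluded as a covariate. It is therefore too strong to say that adjustment happens only when arms differ. But the sentence names no covariate and no occasion, so it does not fix an adjusted primary analysis.
- **The homogeneity branches are introduced as within-group.** If all of them are, that gate does not select the between-arm test. What then remains for the arm comparison is ANOVA or rank tests, chosen by the normality test, with no baseline term stated. If the mixed-model sentence does reach the arm comparison, Step 4 applies. Homogeneity could also mean equal variances; the choice would still be data-driven, but the 1-in-20 figure would not apply.
- **Improvement may mean change from baseline, which uses the baseline value.** This stands as a possible reading. The gain from ANCOVA is then smaller at high correlation (99.0% to 99.7%) and larger at low correlation (78.1% to 93.1%).
- **The article condenses a fuller plan.** Exact model terms may be set there. The point rests on the selection rule that the article does state.

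Three stronger readings are tempting and are not supported. First, a reader might measure the loss at the 4 cm NPC threshold in the Objectives, where 42 per arm give Tukey-adjusted power of 53.0%, rising to 57.6%, 67.3% and 85.2% with adjustment. Those figures compute, but the article does not present 4 cm as the between-arm design difference, and they assume raw follow-up values as comparator. Second, a reader might take intervening variables to mean post-randomisation mediators, whose adjustment would bias the effect. No such variable is named, and the phrase may simply mean confounders. Third, the paired tests might be taken as the evidence of efficacy, but the article does not make them primary.

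**Conclusion.** The point holds in a limited form. The stated rule lets a normality test choose the between-arm method, makes the only explicit baseline adjustment depend on an undefined homogeneity check, and leaves ANCOVA unspecified. The consequence is an analysis not fixed in advance and avoidable loss of precision. It is not a demonstrated bias, and the planned omnibus test is not underpowered on its own assumptions.

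The size depends on ρ, which the documents do not give. On the planned means the gain over unadjusted follow-up is 2.5 percentage points of power at 0.3 (93.1 − 90.6) and 9.1 at 0.7 (99.7 − 90.6). In large samples ANCOVA is never less precise than either the follow-up or the change-score analysis. The 1-in-20 trigger rate and the 6% to 10% recovery rest on reading homogeneity as a 5% between-arm baseline test that governs the arm comparison. The change is worth making but does not threaten the trial's validity.

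**What to change.** Pre-specify one model for each continuous outcome, whatever baseline or normality tests show: a linear mixed model on the 1- and 2-month values with arm, visit, arm × visit, the baseline value of that outcome, and the stratification factors (age, gender, severity of convergence insufficiency). The primary contrasts are the three arm differences at 2 months, with Tukey-adjusted confidence intervals.

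In addition:

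- remove the homogeneity and Kolmogorov-Smirnov tests as selectors and check model residuals instead;
- keep rank-based or bootstrap analyses as sensitivity analyses;
- label paired before-after tests as descriptive;
- state that any ANCOVA covariates are pre-specified baseline variables, and list them.

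The cost is a change of wording in the protocol or analysis plan, made before data are analysed by arm. It needs no extra visits, measurements or patients: the baseline values are already in the schedule and the planned software fits the model. Trial status reports 121 patients randomised, with recruitment continuing, so analysis is a cheaper source of precision than a redesign.
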